# 1. SUMMARY

Patients with inoperable locally recurrent or metastatic breast cancer requiring local radiotherapy will be given local radiation to one tumor site and systemic CP-675,206. Successive cohorts of subjects will be given escalating doses of CP-675,206 in order to determine the maximum tolerated dose of CP-675,206 when given in combination with radiation. The primary endpoint will be toxicity. The secondary endpoints will be clinical and immunological responses. This trial is being conducted as a prelude to a planned phase II trial of CP-675,206 in combination with radiation in metastatic breast cancer.

# 2. INTRODUCTION

## **2.1. Background**

### **2.1.1. Metastatic breast cancer**

Breast cancer is the most common cancer in Canadian women. In 2007 an estimated 22,300 women will be diagnosed and 5300 will die of the disease. Despite advances in therapy, metastatic disease remains an incurable illness, with a median survival of only 2 years. Standard systemic treatment options for metastatic disease include chemotherapy (taxanes, anthracyclines, capecitabine, vinorelbine, gemcitabine) or hormonal therapy (tamoxifen, aromatase inhibitors). Radiation is frequently used in the metastatic setting for palliation of symptoms, with the most frequent site of radiation being bone. Response rates to first line chemotherapy are in the range of 30%, however these responses are not durable. Currently there are no curative options for metastatic disease, underscoring the need for novel therapeutic approaches.

CTLA4 is a receptor expressed on the surface of activated T cells and regulatory T cells. Since signalling through CTLA4 negatively regulates T cell activity, blockade of CTLA4 has emerged as a potential therapeutic strategy to enhance anti-tumor T cell responses (1). CTLA-blockade has been tested in clinical trials using humanized monoclonal antibodies, and some biological responses have been reported. The anti-tumor immune response may be further augmented by the combination of CTLA4-blockade with radiation, with the potential to mediate regression of metastases outside of the field of radiation. The primary goal of this study therefore is to establish the safety of CTLA4-blockade using the antibody CP-675, 206 in combination with radiation. This trial is being conducted as a prelude to a planned phase II trial of CP-675,206 in combination with radiation in metastatic breast cancer.

## **2.2. CP-675,206**

*Additional information can be found in the CP-675,206 Investigator’s Brochure.*

CP-675,206 is a fully human monoclonal antibody (mAb). It binds to the CTLA4 molecule, which is expressed on the surface of activated T lymphocytes and T regulatory cells. The binding of CTLA4 to its target ligands (B7-1 and B7-2) provides a negative regulatory signal, which limits T-cell activation. CP-675,206 antagonizes binding of CTLA4 to B7 ligands and enhances human T-cell activation as demonstrated by increased cytokine (interleukin-2, interferon-) production in vitro in whole blood or peripheral blood mononuclear cell cultures. CP-675,206 is thought to stimulate patients’ immune systems to attack their tumors by blocking the negative regulatory signal of CTLA4.

There is emerging evidence that T regulatory cells may play a role in cancer progression or may present a barrier to immunotherapy (2). Increased numbers of T regulatory cells with an immune suppressive phenotype have been observed in the peripheral blood of patients with cancer, including breast cancer (3). Thus, blocking CTLA4 function on T regulatory cells may also result in enhanced immunotherapy.

In patients, CP-675,206 exhibits a biphasic PK profile following IV infusion. The mean systemic exposure parameters (maximum plasma concentrations [Cmax] and area under the plasma concentration-time curve [AUC]) increase with dose in an approximately proportional manner. Based on the data collected from the single dose phase 1 Trial A3671001, CP-675,206 has a low clearance (0.132 mL/h/kg), a small volume of distribution at steady state (81.2 mL/kg), and a long terminal half-life (22.1 days). These values are consistent with those of natural IgG2.

The anti-tumor activity of antibodies to CTLA4 has been demonstrated in a variety of murine tumor models. In 1996, enhancement of antitumor immunity by CTLA4 blockade was shown for the first time in mice. Here, in vivo administration of antibodies to CTLA4 resulted in the rejection of tumors, including pre-established tumors. In addition, this rejection resulted in immunity to a secondary exposure to tumor cells, suggesting that blockade of the inhibitory effects of CTLA4 can allow for, and potentiate, effective immune responses against tumor cells (4).

CTLA-blockade has been tested in clinical trials using humanized monoclonal antibodies, and some biological responses have been reported. For example, tumor necrosis and vitiligo have been observed using the antibody MDX-010 (5), and a 14% objective response rate was reported from a study with 198 patients with melanoma or renal cell carcinoma (6). The antibody CP-675,206 has been shown to induce durable tumor responses in patients with metastatic melanoma in Phase 1 and Phase 2 clinical studies (7, 8, 9). For instance, in a dose escalation study using CP-675,206, 39 patients, mostly with melanoma, were treated with one dose between 0.01 and 15mg/kg. Two complete responses and 2 partial responses were observed (9).

Since CTLA4-blockade is not dependent on vaccination with specific tumor antigens, this approach may also be effective in different types of cancer, including breast cancer. Furthermore, combining CTLA4-blockade with other therapies that impact anti-tumor immunity, such as radiation therapy, may enhance clinical responses.

## **2.3. CP-675,206 – Clinical Experience**

### **2.3.1. Summary**

CP-675,206 is an investigational agent, and its safety profile has not been fully established. As of August 27, 2006, the safety database is comprised of data from 454 patients treated in completed and ongoing studies.

Single-agent CP-675,206 has shown early evidence of efficacy in patients with melanoma, when administered both as a single dose and in the multiple dose setting.

### **2.3.2. Single-agent, Single Dose Study (A3671001)**

Study A3671001 enrolled a total of 44 patients. At study entry 1 patient (2.3%) had a colorectal tumor, 39 patients (88.6%) had melanoma, and 4 patients (9.1%) had urethral or kidney tumors. All patients enrolled were analyzed for AEs. Dosing: Cohorts of at least 3 patients were recruited for each dose level in the escalation sequence of CP-675,206 from 0.01 to 15 mg/kg. Study Discontinuations: All patients completed the single-dose study. There were no treatment-related AEs leading to discontinuations.

#### 2.3.2.1. Trial A3671001 - Safety

The most frequently observed treatment-emergent, all-causality AEs (in ≥10% of patients) were rash (29.5%), nausea (27.3%), diarrhea (27.3%), fatigue (25.0%), pruritus (22.7%), headache (18.2%), asthenia (13.6%), vomiting (13.6%), fever (11.4%), peripheral edema (11.4%), weight loss (11.4%), dizziness (11.4%), and anemia (11.4%). The incidence of rash, pruritus, and diarrhea appeared to increase with dose. Hyperthyroidism was possibly immune-mediated as evidenced by alteration in autoantibodies. Other possible immune-mediated events, such as skin hypopigmentation/vitiligo, psoriasis, hypophysitis, and alterations in pituitary activity, had no direct evidence of the mechanism of toxicity.

Treatment-emergent, treatment-related CTC Grade 3 events were limited to diarrhea (1 patient each at 6 and 10 mg/kg and 2 patients at 15 mg/kg), rash (1 patient at 15 mg/kg), enzymatic alteration (1 patient with elevated lipase at 10 mg/kg), and asthma (1 patient with pre-existing history at 10 mg/kg). Three CTC Grade 4 events were reported (respiratory arrest, respiratory failure, and malignant melanoma). In all cases, the cause for the CTC Grade 4 event was not the study drug.

#### 2.3.2.2. Trial A3671001 - Efficacy

When administered, as a single agent, CP-675,206 has been found to be associated with clinical activity in patients with metastatic melanoma (7, 8, 9).

In the single dose setting of trial A3671001, which treated primarily melanoma patients, 4 patients had objective responses (one complete response (CR) out of 3 patients treated at 3 mg/kg, one partial response (PR) out of 11 patients treated at 10 mg/kg, and one PR and one CR out of 6 patients treated at 15 mg/kg).

### **2.3.3. Phase I-II, Single agent, Multiple-Dose Study (A3671002)**

*Note: This information is included in this Study Protocol for completeness, although this trial will utilize CP-675,206 in a single dose.*

The single-agent, multiple-dose experience is limited to the ongoing Study A3671002. The phase 1 portion of study A3671002 was designed to assess the safety and tolerability of escalating doses of CP-675,206, to determine the pharmacokinetic-based recommended Phase 2 dose. The Phase 2 portion of the A3671002 trial (multiple dosing) randomized eligible patients to receive either CP-675,206 at 10 mg/kg every 28 days (Arm A) or 15 mg/kg every 90 days (Arm B). According to the database of August 27, 2006, 89 patients were enrolled and treated in the trial, 44 in Arm A and 45 in Arm B. Enrollment was completed in November 2005 and 2 patients remain active on-trial.

Diarrhea was the most frequent Grade 3 adverse event requiring medical intervention. Occasional biopsies of the colon taken at the time of diarrhea have indicated lymphocytic infiltration in the lamina propria or a composite picture resembling inflammatory bowel disease, and there have been diagnoses of colitis confirmed by biopsy. CT scans of the abdomen and a PET scan have shown bowel wall thickening. Although the mechanism behind the development of diarrhea is not clearly understood, there is an, as yet incompletely characterized, potential inflammatory component to the diarrhea, with a colitis that is histologically similar to inflammatory bowel disease (IBD). A suggested Diarrhea Management Guideline is provided within this protocol.

Important safety characteristics of both arms are presented below Fewer SAE’s, serious toxicity and trial discontinuations are associated with administering CP-675,206 at a dose of 15 mg/kg every 3 months.

#### 2.3.3.1. CP-675,206 (10 mg/kg Every 28 Days) – Safety Profile

Of the 44 patients treated with this dose and schedule, 7 (15.9%) were reported with Grade 3 diarrhea. Other Grade 3 toxicities included 3 patients (6.8%) with dehydration, 2 patients (4.5%) with colitis, 1 patient each (2.3%) with perforation of the colon, pancreatitis, arthralgia, arthritis, shoulder pain, rash, and skin exfoliation.

In more than 20% of patients, diarrhea (31.8%), nausea (20.5%), fatigue (22.7%), pruiritis (27.3%) and rash (approximately 41%) were reported. In 5 to 20% of patients, constipation (4.5%), dyspepsia (4.5%), vomiting (11.4%), fever (6.8%), decreased weight (4.5%), dehydration (4.5%), muscle spasms (6.8%), myalgia (9.1%), headache (4.5%), skin exfoliation (9.1%) and transient acantholytic dermatosis were reported.

To date, one patient has exhibited a hypersensitivity reaction shortly after the start of infusion exhibiting periorbital edema and non pruritic rash that were relieved by antihistamine. This patient experienced a similar reaction during rechallenge with CP-675,206 that was again relieved by antihistamine. The patient was then withdrawn from the trial.

#### 2.3.3.3. CP-675,206 (15 mg/kg, every 3 Months) – Efficacy

This regimen has been found to be associated with clinical activity in studies in which CP-675,206 was administered to patients with metastatic melanoma. In the phase II trial A3671002, the clinical efficacy associated with dosing 15 mg/kg every 3 months is similar to the efficacy of dosing 10 mg/kg monthly. 3/43 objective responses (CR and PR) were observed in the former group and 4/41 objective responses have been observed in the latter group.

## **2.4. Rationale**

### **2.4.1. Rationale for combining local radiation with CTLA-4 blockade**

Immunotherapeutic strategies, including CTLA-4 blockade, are aimed at inducing the immune response against tumor cells. This response may be augmented by combination with radiation. There are many potential mechanisms by which radiation therapy may enhance the effect of immunotherapy. For example, the direct induction of tumor cell death by radiation and the subsequent release of tumor antigens may augment the activation of tumor-specific T cells. Other effects of radiation on the tumor microenvironment may also lead to enhanced T cell priming and anti-tumor activity. Radiation has been shown to induce the upregulation of many molecules on human tumor cells, such as Fas/CD95 (10), B7.2 (11) and MHC class I (12) as well as adhesion molecules such as ICAM-1, VCAM-1 and P-selectin (13, 14, 15). In addition, pro-inflammatory cytokines are induced, such as IFN- (16). Novel proteins are induced upon irradiation, which, together with an increase in the intracellular generation of peptides, may lead to an expanded repertoire of responding T cells (17). Importantly, increases in T cell activation in the local milieu and local draining lymph nodes as a result of combination therapy can result in increased circulation of activated tumor-specific T cells and tumor regression at distant, non-irradiated tumor sites.

Studies in various murine cancer models have demonstrated the synergistic effect of combining immunotherapy with local radiation. A model of mammary carcinoma was used to investigate the combination of irradiation of the primary lesion with systemic CTLA-4 blockade (18). This regimen resulted in greatly delayed tumor growth, increased animal survival, and a decrease in lung metastases compared with either intervention alone. The anti-tumor response was dependent on CD8+ T cells, and CTLs specific for the tumor cells could be detected in the spleen following treatment. Many other studies combining local radiation with other immunotherapeutic strategies in mice have also demonstrated a synergistic effect of combination therapy (17, 19, 20, 21, 22, 23, 24).

The anti-tumor activity induced by these combination therapies was shown to be dependent on T cells, and in some cases even antigen-specific responses could be detected (19, 20, 23).

Thus, there is strong pre-clinical evidence that combining radiation therapy and immunotherapy (including CTLA4-blockade) may result in enhanced anti-tumor immune responses and systemic tumor regression. Therefore it is appropriate to study this combination therapy in humans, particularly in patients with incurable disease and very limited treatment options.

### **2.4.2. Rationale for the radiation therapy dose**

Subjects will receive 2000cGy at one tumor site, in 5 daily fractions. This dose induces significant tumor cell death in the majority of tumors, and should provide the appropriate signals for potentially enhancing the anti-tumor T cell response induced by CP-675,206. This is also the standard dose for palliation of metastatic tumors and is associated with a low risk of toxicities.

### **2.4.3. Rationale for the timing of CP-675,206 administration**

Subjects will receive radiation therapy in 5 daily fractions. On the third day of radiation, subjects will also be given one dose of CP-675,206 intravenously. The effect of radiation on promoting cross-presentation of tumor antigens and upregulation of MHC molecules can occur as early as one day after radiation (17). This cross-presentation will induce T cell activation and subsequent CTLA4 upregulation. CTLA4 upregulation on activated effector T cells is detectable 2 days after an antigenic signal (25). Thus, administration of CP-675,206 on the third day of radiation therapy should maximize the potential for CP-675,206 to enhance T cell responses specific for breast tumor-associated antigens. In addition, since the half-life of CP-675,206 in vivo is 22 days, it will still have the potential to synergize with any radiation-induced enhancement of anti-tumor immunity in the days and weeks following dosing. Indeed, the immune-enhancing effects of radiation have been observed at both early and late timepoints after radiation (26).

## **2.5. Future directions**

As described above, the combination of radiation therapy and immune-activating agents such as CP-675,206 has the potential to induce effective anti-tumor T cell responses leading to systemic tumor regression. The clinical efficacy of this combination therapy needs to be investigated in a phase II trial. Thus, the current trial is designed to provide safety data and determine the recommended phase II dose.

The planned study population for our phase II clinical trial will be enriched for patients with so called “triple negative” (ER- PR- HER2-) breast cancers. While considerable progress has been made in the development of targeted therapy for those with hormone receptor and HER2 positive disease, there is now considerable interest in the development of strategies to help patients with so called “triple negative” breast cancer. While these patients may only represent approximately 15% of all breast cancer patients, they have more limited treatment options and poorer clinical outcomes than patients with other breast cancers (27, 28).

Although combined radiation and immunotherapy could potentially lead to tumor regression in most types of breast cancer patients, recent data from triple negative breast cancers suggest that enhanced immunotherapy could have a particularly marked impact on these patients.

The rationale behind this hypothesis is that triple negative breast cancers and medullary breast cancers share basal-like histological features (29, 30) and gene expression profiles (30). Strikingly, medullary breast cancers have both an improved prognosis and immune cell infiltrates (31, 32, 33, 34). Supervised analysis of microarray data has been done to compare basal medullary breast cancers with basal ductal breast cancers (30). In this analysis, most of the genes overexpressed in medullary breast cancers were immune response genes; in particular, those associated with cell-mediated immune responses. Given these features of medullary breast cancers, it is possible that other breast cancers that share basal-like features, including basal-associated antigens (such as triple negative breast cancers) may be particularly amenable to immunotherapeutic strategies. The prediction is that enhancing immunotherapy by combining it with radiation therapy could result in a “conversion” of triple negative breast cancer into a disease with the favorable immune infiltrates and prognoses similar to those associated with medullary breast cancers.

Ultimately, the addition of CP-675,206 to a radiation treatment regimen could prove to be an exciting treatment option for patients with all types of breast cancer, for whom adjuvant radiation therapy is now standard of care. Therefore, we hope to rapidly move from phase I testing to other scenarios.

The Princess Margaret Hospital is the third largest comprehensive cancer center in North America with a long established history of excellence in clinical trials. The Medical Oncology division sees approximately 500 new breast cancer patients each year and Radiation Oncology sees 1200 new breast cancer patients each year. This trial will be conducted in collaboration with scientists from The Campbell Institute for Breast Cancer Research and the Ontario Cancer Institute at PMH, who have expertise in basic and translational immunology. The dedication of the multidisciplinary team involved in this trial will ensure the successful completion of this and future trials.

##

## **Timeline**

| Submission of protocol to Pfizer Canada | Sept 2007 |
| --- | --- |
| Submission of protocol to Pfizer Global | Nov 2007 |
| Expected date of funding approval | Dec 2007 |
| Institutional REB approval, Contracts, Health Canada CTA | April 2008 |
| First patient entered | May 2008 |
| Final patient entered | July 2009 |
| Results available | Nov 2009 |

# 3. TRIAL OBJECTIVES

## **3.1. Primary Objective**

To define the safety, tolerability and maximum tolerated dose (MTD) of CP-675-206 in combination with radiation therapy. This trial is being conducted as a prelude to a planned Phase II trial of CP-675,206 in combination with radiation in metastatic breast cancer.

## **Secondary Objectives**

To monitor for evidence of clinical efficacy of CP-675-206 in combination with local radiation.

To monitor for evidence of immunological responses following administration of CP-675-206 in combination with local radiation.

# 4. TRIAL DESIGN

## **4.1. Overview**

This is a Phase 1, open-label, non-randomized dose escalation clinical trial evaluating the safety and tolerability of escalating doses of CP-675-206 combined with local radiation therapy in patients with incurable locally advanced or metastatic breast cancer. Subjects will receive one treatment cycle on this trial.

Subjects will be given 2000cGy of external radiation in 5 daily fractions at one tumor site using 6-18 MV photons. On the third day of radiation, subjects will also be given one dose of CP-675,206 intravenously.

Patients will be evaluated for toxicities at the following dose levels of CP-675,206: 3, 6, 10 and 15mg/kg. Dose escalation will proceed until the MTD is identified or up to the 15 mg/kg dose level. A minimum of six subjects will be treated with the MTD in order to characterize toxicities and responses.

The estimated maximum number of subjects that will be needed to achieve the trial objectives is 32 patients (range: 6-32 subjects; refer to section 10.2: Sample Size Determination).

## **Dose Escalation Rules**

To minimize the risk of this combination to patients, dosing in the first dose level cohort only will proceed by evaluating safety in the first patient for 12 weeks after the dose of CP-675,206. Prior CP-675,206 single-agent data on safety findings from Pfizer studies indicate that a 6-week follow-up interval was appropriate. However, in order to monitor for potential late-onset toxicities due to the combination of CP-675,206 with radiation, this protocol will follow patients for 12 weeks.

Dosing will be conducted in subsequent dose level cohorts of at least 3 patients, with patients assigned to a dose group after verification by the Investigator of eligibility.

Safety considerations in a current dose level will be assessed as follows to determine dose level escalation:

**1.** If no patient experiences a DLT in the first 12 weeks, the trial will proceed to the next dose level cohort

**2.** If 1/3 patients experiences a DLT in the first 12 weeks, expand cohort to 3 additional patients, and then determine:

- 1. • If 1/6 patients experiences a DLT in the first 12 weeks, escalate to the next dose level.
  2. • If ≥2/6 patients experience a DLT in the first 12 weeks, the current dose level will be considered above the maximum tolerated dose and dose escalation will be discontinued.

**3.** If ≥2/3 patients experience a DLT in the first 12 weeks, the current dose level will be considered above the MTD and the preceding dose level cohort will be expanded to a minimum of 6 patients.

The dose escalation will end after DLT is observed in ≥2 out of 3-6 patients treated at any dose level or after 6 patients at the highest dose level defined (CP-675,206, 15 mg/kg) have completed the 12-week observation period.

Additional patients may be entered as needed at any dose level, including intermediate dose levels, to more fully elucidate the pattern of toxicity and/or better define the MTD.

## **4.3. MTD Evaluable Patient - Definition**

All patients who are able to receive 1 dose of CP-675,206 and complete all 5 fractions of radiation will be deemed MTD evaluable.

Note: While patients will be considered MTD evaluable at the end of the 12-week observation period, dose escalation will occur only when all patients in the cohort have been observed for a full 12 weeks.

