## **4.4. Dose Limiting Toxicities**

Adverse events and other symptoms will be graded according to the NCI Common Terminology Criteria for Adverse Events version 3.0. (<http://ctep.cancer.gov/reporting/ctc.html>).

Dose-limiting toxicity (DLT) is defined as any of the following when considered related to CP-675,206 therapy:

1. • Any CTC Grade 4 treatment related toxicity of any duration.
2. • Other Grade 3 or greater toxicities that do not recover to ≤ Grade 1 or baseline within 7 days of maximal management
3. • Grade 2 or greater treatment related clinical autoimmune toxicity of critical organs, which are defined as lung, heart, kidney, bowel, bone marrow and nervous system, including the eye (except anterior uveitis).

Assessment of DLTs during the first 12 weeks after CP-675,206 dosing will be completed to determine the next dose level.

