### **6.1.3. Patient Dose Modifications (Radiation Therapy)**

If the patient exhibits excessive toxicities, the last treatment or two may be omitted. The dose per treatment is not normally modified.

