### **6.1.4. Management of CP-675,206 Toxicity**

CP-675,206 is an immune modulator, so Investigators should be alert for the development of immune-mediated side effects.

The majority of the adverse events reported in early phase trials have been manageable and well tolerated. The most common treatment-emergent, treatment-related adverse event is diarrhea. Diarrhea typically developed 1 to 2 months after the first dose of CP-675,206 (range: 4-72 days).

Although CP-675,206 is a fully human monoclonal antibody, immunogenicity remains a possibility, and thus acute hypersensitivity reactions such as urticaria, pruritus, laryngeal edema, angioedema, bronchospasm, respiratory distress, nausea, vomiting, abdominal cramps and pain, acute back pain, fever, diarrhea, hypotension and fatal anaphylactic shock, as well as sub acute reactions, are also possible. Possible immune-mediated disorders observed involve the skin (vitiligo and cutaneous leukocytoclastic vasculitis), the thyroid gland (autoimmune thyroiditis), the liver (autoimmune hepatitis), the pituitary (hypophysitis) and bone marrow (immune thrombocytopenic purpura). Abnormal lab results that may be immune-mediated include elevations of serum lipase and amylase and liver function tests. There has been one report of treatment-related uveitis, which resolved within 48 hours after treatment with topical steroids. Across all studies, toxicities generally recovered within 12 weeks, allowing continuation of treatment.

If a patient has an adverse event that is thought to be potentially immune-mediated (other than vitiligo), the Investigator should send a blood sample for autoimmune antibody testing.

CP-675,206 is a monoclonal antibody of the IgG2 type, and it is expected that it would cross the placenta if administered to a pregnant woman and could be secreted in breast milk of a lactating woman. The effect of exposure of a fetus or newborn to CP-675,206 is unknown. Women of childbearing potential must agree to use contraception during this trial and for 12 months after the last dose of CP-675,206.

*Note:* In general, it is not expected that the combination of CP-675,206 with this radiation dose will increase CP-675,206-related toxicities. However, radiation of the sites that are the most common autoimmune targets following CP-675,206 administration will be avoided when possible.

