### **6.1.5. Management of Hypersensitivity Reactions**

In case of hypersensitivity reactions, the Investigator should institute treatment measures deemed medically appropriate. The following treatment recommendations may be applicable and can be adopted at the Investigator’s judgment:

| **Hypersensitivity reaction:** | **Treatment recommendations:** |
| --- | --- |
| CTCAE v.3.0 Grade 1 Allergy (transient flushing or rash, drug fever <38°C) | • Supervise at the bedside. |
| CTCAE v.3.0 Grade 2 Allergy (urticaria, drug fever ≥ 38°C, and/or asymptomatic bronchospasm) | - 1. • Interrupt the infusion of CP-675,206 and disconnect infusion tubing from patient;   2. • Administer IV antihistamines (diphenhydramine, 25-50 mg, and ranitidine, 50 mg, or cimetidine, 300 mg);   3. • After recovery of symptoms, resume the infusion at half the initial infusion rate. If no further symptoms appear, complete the administration of the dose. If symptoms reappear, stop infusion and discontinue patient from the trial. |
| CTCAE v.3.0 Grade 3 or 4 Allergy (symptomatic bronchospasm requiring parenteral medication(s) with or without urticaria; allergy-related edema/angioedema; hypotension; anaphylaxis) | - 1. • Stop the infusion of CP-675,206 and disconnect infusion tubing from patient;   2. • Administer epinephrine (1:10,000) in 3.5 to 5 mL IV boluses (no more than 6 doses);   3. • Administer IV antihistamine (diphenhydramine 50 mg IV push);   4. • If wheezing persists: 0.35 mL of nebulized albuterol or other bronchodilators;   • Consider methylprednisolone 30 to 60 mg IV push, which may prevent recurrent or ongoing reactions; |

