# 10. DATA ANALYSIS/STATISTICAL CONSIDERATIONS

## **10.1. Trial Populations**

The following population will be assessed: An as-treated population, defined as all patients enrolled in the trial that received radiation therapy and one dose of CP-675,206.

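### The MTD-evaluable definition in section 4.3 can exclude a patient with an early DLT whose radiation or infusion was cut short, which biases the DLT count toward escalation

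*Protocol*

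**What the plan says.** Section 4.3 defines who counts toward the MTD: "All patients who are able to receive 1 dose of CP-675,206 and complete all 5 fractions of radiation will be deemed MTD evaluable". The note beneath it places the judgement at the end of the 12-week observation period and holds escalation until the whole cohort has been observed for that time. It does not mention a patient who has a DLT before finishing treatment.

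Two other sections let treatment be cut short because of toxicity:

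- Section 6.1.3, on radiation: "If the patient exhibits excessive toxicities, the last treatment or two may be omitted".
- Section 6.1.5, on Grade 3 or 4 allergy: "Stop the infusion of CP-675,206 and disconnect infusion tubing from patient". For Grade 2 allergy that recurs when the infusion is resumed: "If symptoms reappear, stop infusion and discontinue patient from the trial".

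The order of treatment is set in section 4.1: "On the third day of radiation, subjects will also be given one dose of CP-675,206 intravenously". DLTs are defined in section 4.4 and include "Any CTC Grade 4 treatment related toxicity of any duration", provided the event is related to CP-675,206.

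The escalation rules in 4.2 and the MTD rule in 4.5 refer to patients, patients treated, or a subject. Neither uses the term defined in 4.3. Section 10.2 allows for 2 non-evaluable subjects but gives no replacement rule. The only analysis population, in 10.1, is "all patients enrolled in the trial that received radiation therapy and one dose of CP-675,206".

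**The concern.** Whether a patient is evaluable should not depend on the outcome being counted. Here it can. The fractions that may be dropped for toxicity come after the drug, and an infusion may be stopped because of a reaction to the drug. A patient with an early DLT can thus fail the 4.3 definition because of that DLT.

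If she is then left out and replaced, the DLT rate among those who count is lower than the true rate. The error runs one way, toward escalation and an MTD set too high. The MTD is part of the primary objective and is meant to feed a planned phase II trial. With cohorts of 3 to 6, one misclassified patient is enough to change a decision.

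**Working it through.** **1. Can a DLT make a patient non-evaluable?**

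- *Omitted fraction.* The drug is given on day 3, so fractions 4 and 5 both follow it. By Table 2 they fall on days 4 and 5, which is 1 to 2 days after the dose. Section 6.1 also permits a Tuesday start; fraction 5 then falls on the following Monday, 4 days after the Thursday dose. A drug-related DLT in that window could lead to an omission, and the patient would not have completed all 5 fractions.
- *Stopped infusion.* A related Grade 4 reaction is a DLT whatever its duration, and 6.1.5 has the infusion stopped. The protocol does not say whether a part-given infusion counts as one dose.

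So the path exists. No sentence closes it by keeping DLT patients evaluable.

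**2. Effect of one patient under the rules in 4.2**

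Suppose one DLT patient is excluded and replaced by a patient without a DLT:

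| All DLTs counted | Decision | After exclusion and replacement | Decision |
| --- | --- | --- | --- |
| 1/3 | Add 3 patients | 0/3 | Escalate |
| 2/3 | Dose above the MTD | 1/3 | Add 3 patients |

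**3. Reproducing the plan's figures (section 10.3)**

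Escalation follows 0/3 or 1/6 with DLT. For a true DLT rate p:

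P(escalate) = (1−p)³ + 3p(1−p)² × (1−p)³

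- p = 0.30: 0.343 + 0.151 = 0.494 (stated 0.49).
- p = 0.40: 0.309 (stated 0.31).
- p = 0.50: 0.172 (stated 0.17).

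All nine tabulated values reproduce. They assume that every DLT is counted.

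**4. Effect on the operating characteristics**

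Let f be the share of DLT patients who become non-evaluable and are replaced. The protocol gives no value, so f is an assumption. The DLT rate among evaluable patients is

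q = p(1−f) / (1−pf)

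and P(escalate) is evaluated at q. With f = 0.10:

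- p = 0.30: q = 0.27/0.97 = 0.278. P(escalate) = 0.376 + 0.163 = 0.539, against 0.494.
- p = 0.40: q = 0.36/0.96 = 0.375. P(escalate) = 0.351, against 0.309.

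The probability of at most 1 DLT in 6 patients (the count part of the MTD rule) at p = 0.30 rises from 0.420 to 0.468.

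To show the range, at p = 0.30 the formula gives 0.61 for f = 25% and 0.76 for f = 50%.

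**5. Which values of f fit the protocol?**

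If 30% of 32 patients had a DLT, the expected number made non-evaluable by this route would be 32 × 0.30 × f. That is about 1.0 for f = 10%, 2.4 for f = 25% and 4.8 for f = 50%. Section 10.2 allows for 2 from all causes. On timing, section 6.1.4 reports: "Diarrhea typically developed 1 to 2 months after the first dose of CP-675,206 (range: 4-72 days". Most immune toxicity would therefore appear after the fifth fraction and could not cause an omission. Both points favour the low end.

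**The case against.** The strongest reply is that nothing in 4.2 or 4.5 tells the investigator to drop such a patient. One sentence of 4.2 counts patients treated, and 4.5 separately refuses the MTD to any dose at which a subject has a life-threatening event. On that reading a Grade 4 infusion reaction blocks the dose anyway. This stands in part. The text does not prove that DLT patients are removed, only that they can be. But section 4.3 has no purpose other than to say who counts toward the MTD, and 10.2 expects some patients not to. The life-threatening-event clause acts only when the MTD is named. It is absent from the escalation rules and does not cover other DLTs.

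A reader might infer more than the documents support:

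- *That the most toxic patients as a group leave the count.* Only toxicity within about 1 to 4 days of dosing can cost a fraction. Late toxicity is still counted.
- *That the recurrent Grade 2 allergy rule loses DLTs.* Under 4.4 a Grade 2 allergy is not a DLT in itself, and a Grade 3 reaction that recovers to Grade 1 or baseline within 7 days is not one either. The infusion route matters mainly for Grade 4 reactions or Grade 3 reactions that do not recover.
- *That 4.3 ignores follow-up.* Its note ties evaluability to the end of the 12 weeks. What is missing is a rule for replacing a patient who leaves early without a DLT.
- *That patients who omit fractions vanish from the safety analysis.* Section 10.1 does not require 5 fractions. Only patients with a partial infusion are in doubt there.

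**Conclusion.** The point holds as a defect of definition. Sections 4.3, 6.1.3 and 6.1.5 together allow a patient with an early DLT to be classed as non-evaluable, and 4.2 and 4.5 do not settle the denominator. Any resulting exclusion biases the count toward escalation.

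The average effect is probably small. With f = 10%, P(escalate) moves from 0.49 to 0.54 at a true DLT rate of 30%, and from 0.31 to 0.35 at 40%. These figures rest on an assumed f, on replacement of excluded patients, and on the 0/3 or 1/6 rule. The results for f of 25% and 50% show how the formula behaves; nothing in the protocol supports values that high, and the conclusion does not rest on them. What justifies the change is that one patient can alter a cohort decision and that two readers could count the same cohort differently.

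**What to change.** In section 4.3, state that:

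- any patient who starts CP-675,206 and has a DLT within 12 weeks is evaluable and is counted, whether or not the infusion or all fractions were completed;
- only patients without a DLT who did not complete treatment or the 12-week observation are non-evaluable, and these are replaced;
- this set is the denominator in 4.2 and 4.5.

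The second item matters. Counting a DLT-free patient who received only part of the treatment would itself dilute the DLT rate at the nominal dose.

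In section 10.1, make clear that patients with a partial infusion belong to the safety population. Sections 4.2, 4.3, 4.5, 6.1.3, 6.1.5, 10.1 and 10.2 should be reconciled accordingly. No position is taken here on when fractions or infusions should be stopped.

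The cost is wording, and possibly a few replacement patients. Each would need the 12-week observation before the cohort can be judged, and the allowance of 2 in 10.2 should be checked against the new rule. In return, the table in 10.3 describes the design as it will be run.
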